## Abstract

**Background:**

The treatment of ulcerative colitis (UC) patients with moderate to severe inflammatory activity with anti-tumor necrosis factor alpha (TNFα) antibodies leads to a clinical remission rate of 10% after 8 weeks of therapy. However, it must be taken into account that patient selection in clinical trials clearly influences both response and remission rates. An unsatisfactory response to anti-TNFα medication after week 12 often leads to a discontinuation of treatment. The early prediction of clinical response could therefore help optimize therapy and potentially avoid ineffective treatments.

**Objective:**

The aim of this study is to develop an algorithm for optimizing golimumab administration in patients with moderate to severe UC by calculating the probability of clinical response in Week 26 based on data from Week 6.

**Methods:**

The study is designed as a prospective, single-arm, multicenter, non-interventional observational study with no interim analyses and a sample size of 58 evaluable patients. The primary outcome is the prediction of clinical response in Week 26 based on a 50% reduction in fecal calprotectin and a positive golimumab trough level in Week 6.

**Results:**

Enrollment started in October 2014 and was still open at the date of submission. The study is expected to finish in December 2016.

**Conclusions:**

The early identification of patients who are responding to an anti-TNFα antibody is therapeutically beneficial. At the same time, patients who are not responding can be identified earlier. The development of a therapeutic algorithm for identifying patients as responders or non-responders can thus help prescribing physicians to both avoid ineffective treatments and adjust dosages when necessary. This in turn promotes a higher degree of treatment tolerance and patient safety in the case of anti-TNFα antibody administration.

**ClinicalTrial:**

German Clinical Trials Register, Deutsches Register Klinischer Studien DRKS00005940; https://drks-neu.uniklinik-freiburg.de/drks_web/navigate.do?navigationId=trial.HTML&TRIAL_ID=DRKS00005940 (Archived by WebCite at http://www.webcitation.org/6i4Xoo1sH)

## Introduction

### Background

The treatment of ulcerative colitis (UC) patients with moderate to severe inflammatory activity with anti-tumor necrosis factor alpha (TNFα) antibodies leads to a clinical remission rate of 10% (ULTRA1 study, 80/40 mg adalimumab) [1] to 39% (ACT1 study, infliximab 5 mg/kg body weight [2] and SUCCESS study [3]) after 8 weeks of therapy. However, it must be taken into account that patient selection in clinical trials clearly influences both response and remission rates. In addition, the results of these studies are not consistent with those of observational trials with a high degree of target population representativeness. International guidelines therefore recommend that the success of an anti-TNFα therapy beyond the 12-week mark must be predicted as soon as possible in order to adjust or discontinue treatment depending on the clinical situation [1,4-6]. An unsatisfactory response to anti-TNFα medication after Week 12 often leads to a discontinuation of treatment. The early prediction of clinical response could therefore help to optimize therapy and potentially avoid ineffective treatments [7].

In this regard, the PURSUIT study showed that the administration of the new human anti-TNFα immunoglobulin G1 monoclonal antibody golimumab to subjects with moderately to severely active UC induced clinical response in Week 6 after two injections (Weeks 0 and 2) in 51.0-54.9% of patients in a randomized clinical trial, whereas placebo response was 30.3% (*P*<.001) [8].

After 6 weeks, responders in the golimumab group were randomized again to receive either placebo or 50 or 100 mg golimumab doses every 4 weeks for a further 54 weeks. The analysis of clinical response in this trial showed a statistically significant response for golimumab 50 mg versus placebo (*P*<.001) after 54 weeks (47.0% and 31.2% respectively) [9].

### Study Objective

This early Monitoring of Response (MORE) study (DRKS00005940) seeks to achieve a more thorough understanding of therapeutic development in patients with moderate to severe ulcerative colitis receiving regular doses of golimumab. The aim is to develop an algorithm for optimizing golimumab administration in patients with moderate to severe ulcerative colitis by calculating the probability of clinical response in Week 26 based on data from Week 6.

## Methods

### Trial Design

The study is carried out in conformity with the German Medicinal Products Act (Arzneimittelgesetz, AMG) and is a non-interventional study in accordance with the Medicinal Products Act (§ 4 section 23 p. 3 AMG). The study is designed as a prospective, single-arm, multicenter, non-interventional observational study with no interim analyses and a sample size of 58 evaluable patients, for which 61 patients must be recruited.

### Outcomes

#### Primary

The primary outcome is the prediction of clinical response in Week 26 based on a 50% reduction in fecal calprotectin and a positive golimumab trough level of >2.5 μg/ml in Week 6.

Our definition of a clinical response is a reduction in the partial Mayo score by 2 points between baseline and Week 6, or a partial Mayo score of ≤1 in Week 6.

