### Statistics

#### Analysis

Our aim is to study the detection of a positive trough level of golimumab of >2.5 μg/ml and a significant reduction in fecal calprotectin of 50% from baseline in Week 6 as a reliable predictor for clinical response in Week 26 during long-term treatment with golimumab. In this connection, a level between 2.5 μg/ml and 4.3 μg/ml is regarded as being associated with a therapeutic effect of golimumab [8,9].

Statistical analysis is mainly carried out with descriptive methods such as frequency tables, and statistical parameters such as mean, standard deviation, and quantiles. Bar graphs are used for qualitative data and box-and-whisker plots for quantitative data. In addition, inferential statistical analysis is carried out with relevant significance tests and confidence intervals. Missing data are not imputed.

In order to evaluate the primary outcome, the test problem presented in the section on statistical hypotheses is formulated and solved. The test is carried out with a power of 80% and a two-tailed significance level of alpha=.05. Analysis is carried out with a logistic regression model based on the percentage change of fecal calprotectin and golimumab trough levels. In addition, secondary parameters (eg, ATGs, CRP, WBC) are also analyzed to identify further correlations between the data of Week 6 and therapy outcome in Week 26. The aim is to identify further constraints to the statistical model in order to take into account all relevant parameters in the final version of the algorithm. Secondary outcomes are assessed in an explorative way, that is, no pre-formulated hypotheses are tested. The *P* values obtained are thus interpreted according to Fisher’s method: a *P* value is considered a metric value, and the smaller the *P* value, the larger the significance of the corresponding effect. No interim analyses are planned. Data analysis is carried out only once, at the end of the study.

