#### Hypotheses

The following two-tailed test problem is used for the primary outcome:

Hypothesis 0: beta1=0 versus Hypothesis 1: beta1≠0, where beta1 is the coefficient of the logistic regression model, and null hypothesis: H0. There is no correlation between a significant reduction in fecal calprotectin of 50% from baseline in Week 6 and clinical response to therapy with golimumab in Week 26.

Therefore, our research hypothesis, H1, is that there is a correlation between a significant reduction in fecal calprotectin of 50% from baseline in Week 6 and clinical response to therapy with golimumab in Week 26.

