### Schedule of Visits

There are no defined study visits. In the course of the study, the only clinical and laboratory data recorded are those corresponding to standard medical procedure. Data are recorded in the following observational weeks: baseline, 2, 6, 14, 22, and 26. Deviations of +/- 3 days from this documentation schedule fall within the scope of the study protocol. The period until the next examination is subsequently shortened or lengthened accordingly in order to compensate for deviations and maintain the examination rhythm.

The following data are recorded at the initial screening/baseline examination: date of consent, screening date, inclusion and exclusion criteria, personal information (date of birth, sex, height, weight), date of initial diagnosis, information regarding prior anti-TNFα medication, partial Mayo score, laboratory tests (hemoglobin, WBC, platelet, ferritin, CRP, fecal calprotectin, and ATG), and medication (dose of golimumab, cortisone, and azathioprine).

The following data are recorded during each subsequent examination (week 2, 6, 14, 22, and 26) in the course of the study: partial Mayo score, laboratory tests (hemoglobin, WBC, platelet, ferritin, CRP, and fecal calprotectin), and medication (dose of golimumab, cortisone, and azathioprine). In addition, in Weeks 2 and 6, golimumab trough serum levels and ATG are measured.

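### The only definition of clinical response is tied to Week 6, although the objective, analysis and hypotheses all place the primary outcome at Week 26

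*Protocol article*

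**What the plan says.** The Study Objective section of the protocol article describes the aim as "calculating the probability of clinical response in Week 26 based on data from Week 6". The Outcomes section, under Primary, agrees: "The primary outcome is the prediction of clinical response in Week 26 based on a 50% reduction in fecal calprotectin", together with "a positive golimumab trough level of >2.5 μg/ml in Week 6". The Hypotheses section carries the same timing into the test of beta1. The null reads "There is no correlation between a significant reduction in fecal calprotectin of 50% from baseline in Week 6 and clinical response to therapy with golimumab", and the outcome it names is "clinical response to therapy with golimumab in Week 26".

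Directly after the statement of the primary outcome, the article defines clinical response as a "reduction in the partial Mayo score by 2 points between baseline and Week 6, or a partial Mayo score of ≤1 in Week 6". No other definition of clinical response appears in the article.

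The Schedule of Visits section provides for recording "during each subsequent examination (week 2, 6, 14, 22, and 26) in the course of the study: partial Mayo score", so the score needed for a Week 26 outcome is collected.

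**The concern.** The definition of response is the rule by which the dependent variable of the primary model is coded. As written, it takes the Week 6 score in both limbs. The predictors, the fall in calprotectin and the golimumab trough level, are also Week 6 measurements.

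An analyst who follows the definition would regress Week 6 response on Week 6 biomarkers. A significant beta1 would then show that calprotectin and symptoms move together at one visit. It would not show that Week 6 data forecast Week 26 status, which is the purpose of the algorithm.

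The two readings can also differ in who is evaluable. End of Patient Participation states that stopping golimumab ends participation, and the Analysis section states that missing data are not imputed. A patient who stops between Weeks 6 and 26 has an outcome under one reading and may have none under the other.

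If the conflict is left until data are available, the choice between two primary endpoints would be made after the fact.

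**Working it through.** The point concerns the timing of a definition, so the main check is to set the sections side by side.

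| Section of the protocol article | Predictors | Outcome |
|---|---|---|
| Abstract, Objective and Methods | Week 6 | Week 26 |
| Study Objective | Week 6 | Week 26 |
| Outcomes, Primary: statement of the outcome | Week 6 | Week 26 |
| Outcomes, Primary: definition of response | – | **Week 6, both limbs** |
| Statistics, Analysis | Week 6 | Week 26 |
| Statistics, Hypotheses | Week 6 | Week 26 |
| Justifications for Trial Design | Week 6 | Week 26 |

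Only the definition disagrees with the rest, but it is also the only place that says how a patient becomes a responder.

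- Gap between predictor and outcome as intended: 26 − 6 = 20 weeks.
- Gap under the literal definition: 6 − 6 = 0 weeks.

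**Does the correction affect the sample size?** The plan's figure of 58 was reproduced first. The inputs are a response rate of 40% and an odds ratio of 10 (Calculation), 80% of patients with a calprotectin decline (Rationale), and, from the Analysis section, "The test is carried out with a power of 80% and a two-tailed significance level of alpha=.05". The method is a likelihood-ratio test on 1 degree of freedom with one binary predictor. The 40% is taken as the response probability at the mean of the predictor and as the null value.

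1. Slope: b = ln 10 = 2.303.
2. Intercept: a = ln(0.4/0.6) − 0.8 × 2.303 = −2.248.
3. Response with decline: p1 = 1/(1 + exp(−(a + b))) = 0.514.
4. Response without decline: p0 = 1/(1 + exp(−a)) = 0.096.
5. Information per patient: d = 2 × [0.8 × KL(p1, 0.4) + 0.2 × KL(p0, 0.4)], where KL(p, q) = p ln(p/q) + (1 − p) ln((1 − p)/(1 − q)). This gives d = 2 × (0.8 × 0.0264 + 0.2 × 0.2343) = 0.136.
6. Noncentrality for 80% power at two-sided 0.05: (1.960 + 0.842)² = 7.85.
7. N = 7.85/d = 57.74 with unrounded values, rounded up to 58.

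The same method reproduces all nine rows of Table 3. None of its inputs carries a visit. Moving the outcome to Week 26 with the same planning assumptions therefore leaves 58 evaluable patients.

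**The case against.** The strongest reply is that the intended visit is not in doubt. The hypotheses name Week 26, as do the objective, the analysis section and the sentence just before the definition, and the Week 26 score is collected. One sentence conflicts with all the others, so a wording slip is the likeliest explanation. A statistical analysis plan exists (Study Population refers to it) and may already state the rule correctly.

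Much of this stands, and it limits the point in four ways.

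- A reader might infer that the primary analysis, as planned, predicts nothing at Week 26 or leaves Week 26 scores out. The article does not support this, because its hypotheses explicitly concern Week 26. The concurrent analysis follows only if the definition is applied literally. Nor is there evidence that a Week 6 endpoint was chosen on purpose.
- A reader might use the response rates in the Background to measure the difference between the endpoints: 51.0–54.9% at Week 6 and 47.0% after 54 weeks on 50 mg. These do not measure change from Week 6 to Week 26. The later figure is at 54 weeks and comes from re-randomised Week 6 responders, so its denominator differs. The article does not say whether that trial's definition of response matches the one used here.
- A reader might assume that the concurrent Week 6 association must be strong. The Discussion says that calprotectin falls with therapeutic response, but gives no strength of association with the partial Mayo score.
- A reader might object that a fall of 2 points could mean exactly 2, or that a patient entering with a score of ≤1 would count as a responder. The first is a matter of clarity. The second is hypothetical in a population described as having moderate to severe disease. Neither carries the point.

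The reply does not remove the contradiction. The definition is stated, not omitted, so a correct analysis plan would still conflict with it.

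**Conclusion.** The point holds as an internal contradiction in the primary endpoint. The outcome is response in Week 26, while the only rule for deciding response uses Week 6 in both limbs. If that rule is followed, predictor and outcome coincide and the intended 20-week horizon becomes 0. If the hypotheses are followed instead, the prediction is as intended but the endpoint has no stated definition at its own visit. The passages must be reconciled before analysis.

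The article gives no usable figure for how many patients would be classified differently at the two visits, so none is claimed. The conclusion on sample size assumes that the planning values (40% response, odds ratio 10, 80% with decline) are kept; it does not judge whether they suit Week 26.

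**What to change.** Change the visit in both limbs of the definition, for example: *Clinical response in Week 26 is a fall in the partial Mayo score of at least 2 points from baseline to Week 26, or a partial Mayo score of ≤1 in Week 26.* The words *at least* remove the small ambiguity at the same time. No further baseline condition is needed to resolve the contradiction.

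If a Week 6 response variable is wanted, give it a separate name, such as *early response*, so that it cannot be taken for the primary outcome. Check that the analysis plan uses the same rule, and date the change before the analysis.

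The cost is a correction to the wording. The Week 26 partial Mayo score is already in the documentation schedule, no additional data are required, and the calculated 58 evaluable patients stay as they are.

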#### Secondary

In addition to the primary study goal, the following secondary outcomes are analyzed:

1. At which point in time is a 50% reduction in fecal calprotectin a reliable predictor of response?

2. How strong is the correlation between antibody towards golimumab (ATG) level and fecal calprotectin level?

3. How strong is the correlation between ATG and the partial Mayo score?

4. How strong is the correlation between golimumab trough level and fecal calprotectin?

5. How strong is the correlation between golimumab trough level and the partial Mayo score?

6. Do the following parameters exert any influence on clinical response?

      a) C-reactive protein (CRP)

      b) white blood cells (WBC) count

      c) hemoglobin

      d) platelet count

      e) ferritin

7. Frequency of adverse reactions

### Statistics

#### Analysis

Our aim is to study the detection of a positive trough level of golimumab of >2.5 μg/ml and a significant reduction in fecal calprotectin of 50% from baseline in Week 6 as a reliable predictor for clinical response in Week 26 during long-term treatment with golimumab. In this connection, a level between 2.5 μg/ml and 4.3 μg/ml is regarded as being associated with a therapeutic effect of golimumab [8,9].

Statistical analysis is mainly carried out with descriptive methods such as frequency tables, and statistical parameters such as mean, standard deviation, and quantiles. Bar graphs are used for qualitative data and box-and-whisker plots for quantitative data. In addition, inferential statistical analysis is carried out with relevant significance tests and confidence intervals. Missing data are not imputed.

In order to evaluate the primary outcome, the test problem presented in the section on statistical hypotheses is formulated and solved. The test is carried out with a power of 80% and a two-tailed significance level of alpha=.05. Analysis is carried out with a logistic regression model based on the percentage change of fecal calprotectin and golimumab trough levels. In addition, secondary parameters (eg, ATGs, CRP, WBC) are also analyzed to identify further correlations between the data of Week 6 and therapy outcome in Week 26. The aim is to identify further constraints to the statistical model in order to take into account all relevant parameters in the final version of the algorithm. Secondary outcomes are assessed in an explorative way, that is, no pre-formulated hypotheses are tested. The *P* values obtained are thus interpreted according to Fisher’s method: a *P* value is considered a metric value, and the smaller the *P* value, the larger the significance of the corresponding effect. No interim analyses are planned. Data analysis is carried out only once, at the end of the study.

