### Sample Size

#### Rationale

Sample size is planned based on data from studies researching a correlation between fecal calprotectin and response to an anti-TNFα therapy.

De Vos et al [10] describe response rates as: “After 10 weeks anti-TNFα therapy induced endoscopic remission in 63% (confidence interval: 47–78%) of patients”. Molander et al [11] describe the correlation between the predictive quality of fecal calprotectin and the remission rate. The results are displayed in Table 1.

**Table 1 table1:** Cross classification of fecal calprotectin predictive quality and remission.

		Fecal calprotectin decline		Total
		Yes	No	
Remission				
	Yes	30	3	33
	No	6	21	27
Total		36	24	60

Based on these results, the odds ratio (OR) is calculated as OR (30*21) / (6*3)=35. It should be noted that for the above study the cut-off point for fecal calprotectin decline was a reduction of >75% from baseline. Lower cut-off points, for example, a 50% reduction, would lead to smaller OR, as the number of patients with neither decline nor response is described as being almost constant in the above-mentioned literature: “Absence of decrease in calprotectin levels at week 6 identified patients resistant to the treatment” [11]. It is therefore assumed for sample size calculation that 80% of the patients will have a “fecal calprotectin decline.” Table 2 summarizes the scenarios that have been taken into consideration.

**Table 2 table2:** Sample size rationale: Response rates and their effect on resulting OR for 9 different scenarios.

Scenario	Response rate (%)	OR
1	40	10
2	40	20
3	40	30
4	50	10
5	50	20
6	50	30
7	60	10
8	60	20
9	60	30

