#### Calculation

Sample size calculation is carried out with the statistical analysis software SAS. Table 3 shows the required number of evaluable patients for each scenario. It is expected that 5% of the intention-to-treat principle population will be excluded. Sample size is inversely proportional to the OR and the response rate.

**Table 3 table3:** Sample size calculation: Number of evaluable subject and total number of subjects considering dropouts for 9 different scenarios.

Scenario	Response rate, %	OR	Evaluable subjects, n	Subjects including potential dropouts, total n
1	40	10	58	61
2	40	20	40	42
3	40	30	34	36
4	50	10	50	53
5	50	20	34	36
6	50	30	29	31
7	60	10	45	48
8	60	20	31	33
9	60	30	26	28

To prevent study failure due to an underpowered study, a worst case scenario with a response rate of 40% and an OR of 10 is used as a basis for sample size. A total of 58 evaluable subjects are therefore necessary for the trial, thus 61 patients must be recruited.

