## Discussion

### Rationale for the Trial

The early identification of patients who are responding well to an anti-TNFα-antibody is therapeutically beneficial. At the same time, patients who are not responding can be identified earlier. The development of a therapeutic algorithm for identifying patients as responders or non-responders can help prescribing physicians both to avoid ineffective treatments and to adjust dosages when necessary. This in turn would promote a higher degree of treatment tolerance and patient safety in the case of anti-TNFα antibody administration.

There is a clear association between detectable trough levels of anti-TNFα inhibitors and clinical therapeutic response. On the other hand, the detection of anti-drug antibodies is associated with a poor response.

Fecal calprotectin levels reflect mucosal inflammation status. The strong correlation between high fecal calprotectin and mucosal inflammation has been widely described. Furthermore, it is also clear that fecal calprotectin levels decrease if there is therapeutic response.

A regular question among IBD patients is how long they will have to take their medication in total. Yet there is currently insufficient data regarding optimal treatment length with TNFα inhibitors. In view of the elevated costs and possible side effects associated with this type of treatment, it is desirable to clearly define a patient population for which continued therapy is justifiable.

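### The only stated primary criterion is a test of non-zero association, which does not by itself support calling the Week 6 markers a reliable predictor

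*Protocol article*

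**What the plan says.** The Analysis section gives the aim: to study a golimumab trough level above 2.5 μg/ml and "a significant reduction in fecal calprotectin of 50% from baseline in Week 6 as a reliable predictor for clinical response in Week 26". The Study Objective speaks of calculating each patient's probability of response. The Rationale for the Trial states the intended use: "The development of a therapeutic algorithm for identifying patients as responders or non-responders can help prescribing physicians both to avoid ineffective treatments".

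The Analysis section says that the primary outcome is evaluated by solving the test problem in the Hypotheses section, which is "Hypothesis 0: beta1=0 versus Hypothesis 1: beta1≠0". The alternative is worded there as a correlation between a 50% calprotectin reduction at Week 6 and response at Week 26. On error rates: "The test is carried out with a power of 80% and a two-tailed significance level of alpha=.05".

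The sample size serves the same test. The Rationale says: "It is therefore assumed for sample size calculation that 80% of the patients will have a" calprotectin decline. The Calculation section then says that "a worst case scenario with a response rate of 40% and an OR of 10 is used as a basis for sample size", and concludes: "A total of 58 evaluable subjects are therefore necessary for the trial, thus 61 patients must be recruited". The article gives no target, threshold or precision for any measure of predictive performance.

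**The concern.** The question is about prediction in individual patients, while the criterion is about association in the group. A test of beta1=0 asks whether responders are more frequent among patients with a decline than among those without. It does not ask how often a patient with a decline goes on to respond, or what share of non-responders the rule picks out. When most patients are test-positive, as the plan assumes, a large odds ratio can go with a weak positive prediction.

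At stake is how the result is read. A small P value could be reported as confirming a reliable predictor and carried into the algorithm, while the same data show that about two thirds of non-responders had a calprotectin decline.

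**Working it through.** **Inputs.** Share with decline 80% (Rationale); response rate 40%, odds ratio 10, 58 evaluable patients (Calculation); two-sided alpha 0.05 and power 80% (Analysis). The predictor is calprotectin decline, yes or no, as in the Hypotheses section and the sample size.

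**1. Reproduce the plan's figure.** Take 40% as the response probability at the mean of the predictor, so that logit p0 = logit(0.40) − 0.8 × ln(10) = −0.405 − 1.842 = −2.247 and logit p1 = −2.247 + 2.303 = 0.055. This gives p0 = 0.096 (response without decline) and p1 = 0.514 (response with decline). The likelihood-ratio noncentrality per patient is 2 × Σ w[p ln(p/0.4) + (1−p) ln((1−p)/0.6)], with weights 0.8 and 0.2, which is 0.1359. The smallest N with 80% power is 58. The same method returns all nine values of Table 3 (58, 40, 34, 50, 34, 29, 45, 31, 26). That SAS was used in this way is inferred from the match; the article does not say so.

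**2. Two readings of the 40%.**
- Reading A: 40% is the overall response rate, as the text words it. Solving 0.8p1 + 0.2p0 = 0.40 with odds ratio 10 gives p1 = 0.479 and p0 = 0.084.
- Reading B: the parameterisation of step 1. The implied overall rate is r = 0.8 × 0.514 + 0.2 × 0.096 = 0.430.

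**3. Performance of calprotectin decline alone.** PPV = p1; NPV = 1 − p0; sensitivity = 0.8p1/r; specificity = 0.2(1 − p0)/(1 − r); accuracy = 0.8p1 + 0.2(1 − p0).

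| | Reading A | Reading B |
|---|---|---|
| PPV | 47.9% | 51.4% |
| NPV | 91.6% | 90.4% |
| Sensitivity | 95.8% | 95.6% |
| Specificity | 30.5% | 31.7% |
| Accuracy | 56.6% | 59.2% |
| Accuracy if all are called non-responders | 60.0% | 57.0% |
| AUC of the yes/no rule, (sensitivity + specificity)/2 | 0.63 | 0.64 |

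**4. What a significant result could look like.** With 58 patients, 0.8 × 58 ≈ 46 decline and 12 do not. A table close to expectation under Reading A has 22/46 and 1/12 responders. The likelihood-ratio test gives P = 0.007. The 95% Wilson intervals are:
- PPV 22/46: 34–62%
- NPV 11/12: 65–99%
- Specificity 11/35: 19–48%

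**5. Other planning scenarios.** At 40% response with odds ratio 20 or 30, Reading A still gives PPV 49% and accuracy 58–59% against 60%; Reading B gives PPV 55–57% and accuracy 63–65% against 55% and 54%. At 50–60% response, accuracy is 65–78% over both readings and PPV is 59–75%, and the rule beats both trivial rules. For contrast, Table 1, with a cut-off of more than 75% reduction, gives PPV 30/36 = 83%, NPV 21/24 = 88% and accuracy 51/60 = 85%.

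**The case against.** Several objections have force.

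- A reader might infer that the rule is right less often than calling everyone a non-responder. That holds on Reading A but reverses on Reading B, the one that reproduces N=58. The documents support only that the two are about equally accurate.
- The 40%/odds ratio 10 point is described as a worst case, chosen to protect power. It is not a forecast, and most other scenarios look better. This stands, but it is also the case for which the study was sized.
- The figures are for calprotectin alone. The primary outcome also uses trough level, and the model uses percentage change. The article gives no trough rates, so nothing can be said about the accuracy of the combined rule or the AUC of the planned model.
- A reader might also infer that the article equates rejecting beta1=0 with reliability, or treats rejection as grounds for treatment decisions. No sentence says so, and the study is non-interventional. What the text does show is that this test is the only stated criterion for the primary outcome.
- Finding non-responders earlier is a stated purpose, and an NPV of 90–92% serves it. True, but absence of decline flags only 20% of patients and about 31% of non-responders, and the estimate would rest on about 12 patients.
- Accuracy measures may be in the analysis plan, which is not shown; the article foresees descriptive tables and confidence intervals. Their absence from an article is no fault. The point is that the primary criterion the article does state answers a different question from its aim.

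**Conclusion.** The point holds in a limited form. The article sets an aim of reliable prediction and evaluates its primary outcome only by a test of non-zero association. At its own worst-case planning values, a true and significant effect of calprotectin decline goes with a PPV near one half, specificity near 31%, and accuracy between 3.4 points below and 2.2 points above a rule that uses no data. A significant beta1 therefore does not by itself support the term reliable predictor.

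This rests on the stated 80%, 40% and odds ratio 10, with both readings of the 40% shown, and on calprotectin decline as a yes/no marker. It does not show that the combined rule will perform badly, or that calprotectin is useless: as a rule-out signal it could be informative. At 50–60% response the shortfall is smaller.

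**What to change.** Report sensitivity, specificity, PPV and NPV with 95% Wilson intervals, and the AUC, for the Week 6 rule against Week 26 response, both for calprotectin alone and combined with trough level. Make these the primary read-out alongside the beta1 test. Word a significant beta1 as association only, and base any statement on reliability on these estimates and their intervals.

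A mandatory lower confidence bound is not proposed, since intervals as wide as 65–99% for NPV make such a criterion hard to defend with 58 patients. A comparison with the Week 6 partial Mayo score would be of interest, but only once the Primary outcome section, which defines clinical response by the partial Mayo score at Week 6, has been reconciled with the Week 26 endpoint. Until then the comparison would be largely circular.

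Cost: a little more analysis on data already recorded, and a documented change to the primary read-out before the single final analysis. The price is wide intervals and possibly a less favourable conclusion.
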